## Methods

### Data collection, management and analysis

#### Data collection methods

De-nominalized demographic data will be collected by an independent investigator. During the procedure, a standardized data collection document will be used to ensure that all data points are noted and are available for future statistical analysis. For every plexus block, at least two people (operator plus research assistant) will be required for data collection and the research assistant will be responsible for time measurement using a chronometer. Because patient follow up is maintained only up to 48 hours after the surgery, patient retention is not expected to be an issue. Demographic data will include a phone number to allow communication after discharge from the hospital. A presentation to the anaesthesia department and peripheral participating centres will be done to explain the project and pertinent documents.

#### Data management

The patient file number and any additional data allowing patient recognition will be gathered in a different and unique Microsoft Excel file. Every patient will be attributed a number that will correspond to the number in the other data file. These personal data will be on a different locked computer, kept in a locked room at the hospital. These data will be directly transferred from the hand-written form to the locked computer by a research member and will never transit by mail or the Internet. Once the sensitive data are entered onto the computer, any hand-written form allowing participant recognition will be destroyed to avoid the data being divulged. Only research members will have access to the computerized data.

Non-sensitive data will be kept in an Excel folder with a number corresponding to the sensitive data number. A research member will transfer the collected data from the hand-written document to the computerized database. The hand-written document will be kept in case of future need. Back-up data will be kept on the personal computers of the main authors to allow statistical analysis. No related processes to promote data quality will be used, as only research members will be responsible for data transfer from the hand-written document to the computer database. Blocks will be videotaped by recording the screen of the ultrasound device. Patients will not be recorded during these procedures and there will not be any possibility of recognizing the person undergoing the block. Data will be shared by the authors via a password-secured file (Dropbox®) that is only accessible to authors of the study. As soon as the videos are shared between recruiting centres, the videos will be stored in a separate file on the same locked computer as used to store the rest of the information collected.

#### Statistical methods

Analysis of the primary outcome: performance time will be analyzed with a non-inferiority test of the averages, with the objective of finding that the experimental RCB approach takes no longer to perform than the coracoid ICB approach.

The secondary outcomes will all be analyzed using superiority analysis. For continuous data or ordinal data with >8 categories, data will be compiled as average and standard deviation. If data are parametric, Student’s *t* test will be used and if not, the Mann-Whitney test will be used. For dichotomous data (block success, use of neurostimulation), the chi square or Fisher exact test will be used if n >5 or is not >5, respectively. Finally, for ordinal data the chi square test will be used if data are parametric, otherwise the Mann-Whitney test will be used.

Subgroup analysis will be conducted to evaluate if higher BMI influences the outcomes of performance time, needle visibility, number of needle passes and needle angle. Patients will be divided in two groups (of those with higher and those with lower BMI than the average BMI of all recruited patients) and analyzed according to their subgroup. If data are missing or if any patients drop out of the study, data will be analyzed using the intention-to-treat principle.

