## Methods

### Assignment of interventions

#### Allocation: sequence generation

Participants will be randomly assigned to either the control or experimental group with a 1:1 allocation ratio as per a computer-generated randomization schedule stratified by sites using permuted blocks of random sizes. The block sizes will not be disclosed, to ensure concealment. Stratification by site will be of particular interest because in this current pre-trial state, one centre mostly uses the retroclavicular approach while the second one uses the infraclaivuclar approach.

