### Risk of bias

Unfortunately, the proposed methodology implies certain bias that would be hard to eliminate with the current research setup available in the participating centres. First of all, we will have selection bias because we will not be able to approach a consecutive series of patients, as personal resources are not sufficiently available, especially during the on-call hours, when recruitment depends on the anaesthesiologist and their “free” time for recruitment. Moreover, we will have reference centre bias because more anaesthesia providers are competent with RCB in Sherbrooke, and most of the enrolment will be in this university hospital.

For data collection, as it is not possible to double blind this trial for reasons previously described, so we will have performance bias. We might also include attention bias when asking patients if they have discomfort immediately after the plexus block and at 48 hours. However, this approach will be similar and neither group should influence one group more than the other. Finally, we might have therapeutic personality bias as in the consent form we mention our expectation of a shorter and less painful block with the RCB approach. However, we deemed it necessary to mention those facts because they are some of the implied reasons for the implementation of this trial.

For data analysis, we have two principal biases. First, we might have an “all is well in the literature” bias when using the Likert scale to evaluate needle visibility. This scale has been previously used in the similar studies; however, it has never been validated and results should thus be interpreted with caution. Unfortunately, no validated tools exist for this purpose. Furthermore, there might be detection bias even if the outcome assessor for the motor and sensory block is blinded to the procedure. To minimize this we will extend the chlorhexidine application to the two needle insertion points and two bandages will be applied even if no needle was inserted for one of them. However, blood leaking or soaking the bandage might inform the outcome assessor on the approach used.

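### Site is a stratification factor because the two centres habitually use opposite techniques, yet no named test uses site and no by-site result is planned, although most patients will come from the RCB-experienced centre

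*Protocol article*

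**What the plan says.** In Allocation: sequence generation, the protocol article assigns patients 1:1 by a "computer-generated randomization schedule stratified by sites using permuted blocks of random sizes". The reason it gives for stratifying is that "one centre mostly uses the retroclavicular approach while the second one uses the infraclaivuclar approach".

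In Risk of bias, the authors concede a reference-centre bias: "more anaesthesia providers are competent with RCB in Sherbrooke, and most of the enrolment will be in this university hospital". The expected share is not given.

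In Statistical methods, the primary outcome is handled in one sentence: "performance time will be analyzed with a non-inferiority test of the averages". Continuous secondary outcomes get Student's t if judged parametric ("test will be used and if not, the Mann-Whitney test will be used"). Dichotomous outcomes get chi-square or Fisher's exact test, and ordinal outcomes chi-square or Mann-Whitney. One subgroup factor is named, body mass index: "Subgroup analysis will be conducted to evaluate if higher BMI influences the outcomes of performance time".

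Site does not appear in that section as a covariate, a stratum, a subgroup or an interaction.

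**The concern.** Performance time plausibly depends on how familiar the operator is with the technique. The protocol treats habitual technique as important enough to control in the randomisation, then names an analysis that never looks at it again. Two separate things follow.

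- **Precision.** If one centre is slower overall, a two-sample test leaves the between-site spread in the residual variance. The stratification has already balanced that spread across arms, so the reported standard error is too large and the test is conservative.
- **Interpretation.** The pooled difference averages the two site-specific differences, weighted by enrolment. With most patients in Sherbrooke, it mainly describes a centre where RCB is familiar. If RCB were slower where the infraclavicular block (ICB) is routine, no planned result would show it.

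**Working it through.** **Inputs from Sample size.** ICB mean 5 min 36 s = 5.60 min; expected RCB mean 4 min 29 s = 4.483 min; difference d = 4.483 − 5.60 = −1.117 min; SD 2 min 18 s = 2.30 min; margin 5% × 5.60 = 0.28 min; 49 per group; power 0.90; one-sided α 0.05.

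**Assumptions (not in the documents).** Sherbrooke's share w, the gap in mean time between sites, any site-specific effects, and that 2.30 min is a within-site SD.

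**1. The plan's own figure.** n = 2(1.645 + 1.282)² × 2.30² / (0.28 + 1.117)² = 46.4, so 47 per group, or 48 with the t distribution. The stated 49 is reproduced to within two patients. At 49, SE = 2.30 × √(2/49) = 0.465 min and (0.28 + 1.117)/0.465 = 3.006. Power = Φ(3.006 − 1.645) = 0.913.

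**2. Precision lost by leaving site out.** The pooled variance is 2.30² + w(1 − w) × gap².

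| w | Gap (min) | Added variance | SE ratio |
|---|---|---|---|
| 0.8 | 1.5 | 0.36 | √(5.65/5.29) = 1.03 |
| 0.8 | 2.0 | 0.64 | √(5.93/5.29) = 1.06 |
| 0.7 | 1.5 | 0.47 | √(5.76/5.29) = 1.04 |
| 0.7 | 2.0 | 0.84 | √(6.13/5.29) = 1.076 |

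At the worst ratio, power = Φ(3.006/1.076 − 1.645) = Φ(1.149) = 0.875. This is a ceiling on the loss, because it lets the estimate itself vary more. Under site-stratified allocation only the estimated SE grows, which gives Φ(3.006 − 1.645 × 1.076) = Φ(1.236) = 0.89.

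In a simulation at w = 0.8 with a common effect at the margin, the pooled test's type I error was 0.048, 0.045 and 0.034 for gaps of 0, 1.5 and 3 min. The site-adjusted test stayed at 0.048 to 0.054. The error is on the safe side.

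**3. What the pooled difference weights.** Pooled difference = w × d(Sherbrooke) + (1 − w) × d(Quebec). The chance of declaring non-inferiority is Φ((0.28 − pooled)/0.465 − 1.645). With d(Sherbrooke) = −1.117 min:

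| w | Pooled (min) and chance if d(Quebec) = 0 | Pooled (min) and chance if d(Quebec) = +1.117 |
|---|---|---|
| 0.6 | −0.67; 0.66 | −0.22; 0.29 |
| 0.7 | −0.78; 0.74 | −0.45; 0.47 |
| 0.8 | −0.89; 0.81 | −0.67; 0.66 |
| 0.9 | −1.01; 0.87 | −0.89; 0.81 |

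With a common effect of −1.117 min the chance is 0.913 at every split. So if the effects differ by site, the conclusion depends on the enrolment split.

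**4. Whether a site term changes the weighting.** It does not. In the simulation with w = 0.8 and effects of −1.117 and +1.117 min, the pooled and site-adjusted estimates both averaged −0.66 min, and non-inferiority was declared in 0.61 and 0.62 of runs. Equal site weights gave 0.00 min and about 0.12.

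**5. Precision of by-site results.** At 80/20, with 39 and 10 per arm, the 90% CI half-widths are 1.645 × 2.30 × √(2/39) = 0.86 min and 1.645 × 2.30 × √(2/10) = 1.69 min. The interaction SE is 2.30 × √(2/39 + 2/10) = 1.15 min. The equal-weight SE is half of that, 0.58 min, and its power under the planned common effect is about 0.78.

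**The case against.** The strongest reply is that nothing here is invalid. Stratified 1:1 allocation keeps the pooled difference unbiased for the patients enrolled, and omitting site makes a false claim of non-inferiority less likely under a common effect. That stands.

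A reader might infer that the missing adjustment is what tilts the answer towards the RCB-experienced centre. The documents do not support this. The tilt comes from unequal enrolment; with 1:1 allocation within site, an additive site term returns essentially the same estimate. A reader might also infer that the authors expect opposite effects at the two sites, or that RCB would look clearly non-inferior while being slower in Quebec. The protocol says only that habits differ, and even under sign-reversed effects with 80% in Sherbrooke the chance of declaring non-inferiority is 0.61 to 0.66.

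It can also be said that the centre bias is disclosed, that covariates and by-site tables often sit in an analysis plan not shown here, and that the article never calls the analysis unadjusted. These points have weight: the absence of adjustment is inferred from the tests named, and an unseen plan may add site. But Statistical methods is not silent. It fixes a test for each outcome type and names a subgroup factor, and these do not follow through the reason given for stratifying. Disclosing a bias does not analyse it.

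Lastly, by-site estimates will be weak: a half-width of 1.69 min is about six times the 0.28 min margin. That is a reason to keep them descriptive, not to omit them.

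**Conclusion.** The concern holds in a limited form. The analysis as named does not use the stratification factor and offers no view of the result by site.

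The precision cost is modest: an SE about 3 to 8% larger and power of about 0.875 at worst against 0.91, assuming a 1.5 to 2 min gap between sites, 70 to 80% enrolment at one of them, and 2.30 min as the within-site SD. With a smaller gap the loss shrinks towards nothing.

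The interpretive gap is separate and probably matters more. The pooled difference mainly describes the RCB-experienced centre, and how far that matters depends on site-specific effects about which the documents give no figures. There is no bias for the enrolled mix, no inflated type I error under a common effect, and no change to the required sample size.

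**What to change.** - **Primary outcome:** take the upper confidence bound for RCB minus ICB from a linear model with arm and site, and compare it with the stated margin.
- **Secondary outcomes:** use site-stratified tests, such as van Elteren for ranked data and Cochran-Mantel-Haenszel for dichotomous data. Like the site term, these respect the design but do not remove the weighting by enrolment.
- **By-site results:** report the RCB minus ICB difference in performance time with its confidence interval in each site, and the arm-by-site interaction, all labelled descriptive.
- **Conclusion:** limit it to the enrolled mix of sites and report the actual split.
- **Optional:** an equal-site-weight estimate, as a low-power sensitivity analysis only.

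The cost is wording in the analysis section. Site is already known from the randomisation, and no extra patients or data are needed. The downside is imprecision in the smaller site and in the interaction, so the text should say beforehand that a wide interval there is not evidence that the sites agree.

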
#### Participant timeline

A research member will screen the operating list for any eligible patients. When identified, the patient will first be encountered for the presentation of the research project and possible recruitment. This first encounter will be at least one hour before the scheduled surgery time and will be in the surgical day care unit or in the unit in which the patient is hospitalized. When consent is obtained, patients will first complete a demographic questionnaire. They will then be transported to the induction room for the performance of the plexus block, as previously described. Once the block is completed, patients will remain monitored in a suitable area with appropriate surveillance (induction room, operating room (OR), recovery room) until surgery. The independent research assistant will assess the sensory and motor loss at 10, 20 and 30 minutes (see Fig. 1).

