#### Sample size

We decided to conduct a non-inferiority trial with the aim of demonstrating that performance time for the RCB approach is no longer than for the coracoid ICB approach. On the basis of a recent study [15], we established that the performance time for the coracoid ICB approach is 5 min 36 s, with 45 s of visualization time. On the basis of the feasibility trial recently conducted, needling time for the RCB approach is 3 min 42 s [11]. If we use the same imaging time of 45 s, we expect a performance time of 4 min 29 sec for the experimental approach. The standard deviation used for both groups was 2 min 18 s, as reported in the literature [15]. We deemed that a time superiority of 5% would be significant. In other words, RCB performance time will be deemed non-inferior to ICB if the upper margin of the 95% confidence interval created around RCB performance time is under the ICB performance time plus 5%. When using these hypotheses to conduct a non-inferiority analysis, a calculated sample size of 49 patients per group will be required to provide statistical power of 0.90 and one-sided type I error of 0.05. To compensate for potential dropouts or inadequate procedures, we will aim for a sample size of 55 patients per group.

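### The primary time comparison uses neither BMI nor the stratification factor site as a covariate: a missed, probably modest gain in precision, not an error

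*Protocol article*

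**What the plan says.** The protocol article's Statistical methods section states that "performance time will be analyzed with a non-inferiority test of the averages". It assigns the secondary outcomes to two-group tests (Student's t, Mann-Whitney, chi-square, Fisher). No covariate is named for any of them.

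BMI appears in the same section for a subgroup analysis only, whose purpose is to "evaluate if higher BMI influences the outcomes of performance time, needle visibility, number of needle passes and needle angle". The two subgroups consist "of those with higher and those with lower BMI than the average BMI of all recruited patients". The article does not list BMI by name among the items collected. A split at the mean of all recruited patients nevertheless requires it for each of them, and baseline information is gathered before the block (Participant timeline: "When consent is obtained, patients will first complete a demographic questionnaire").

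Allocation follows a "computer-generated randomization schedule stratified by sites using permuted blocks of random sizes". The same section adds that the two centres habitually use different approaches. The Risk of bias section says that more providers are competent with RCB in Sherbrooke and that most enrolment will be there.

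**The concern.** BMI and site are both fixed before allocation takes effect, and both are available at no extra cost. If either is related to performance time within arms, an unadjusted comparison leaves that variation in the error term and the interval is wider than it needs to be. For site there is a further reason: when randomisation is stratified on a factor that predicts outcome, an analysis that ignores the factor tends to overstate the standard error.

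Precision matters here because the non-inferiority margin is small against the noise. It is 5% of 336 s, or 16.8 s, against a standard error of 27.9 s at 49 per group. The same reasoning applies, with less weight, to the arm comparisons of visibility, passes and angle, which the plan also examines against BMI.

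**Working it through.** **Inputs from the Sample size section**
- ICB: "the performance time for the coracoid ICB approach is 5 min 36 s, with 45 s of visualization time", so the mean is 336 s.
- RCB: "we expect a performance time of 4 min 29 sec for the experimental approach", so the mean is 269 s and the planned difference is 269 − 336 = −67 s. The stated components, 3 min 42 s + 45 s, sum to 267 s; the plan's own 269 s is used here.
- SD 138 s in both groups; margin 0.05 × 336 = 16.8 s; one-sided alpha 0.05; power 0.90; 49 per group, 55 with the dropout allowance.

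**Reproducing the plan's figure**

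n per group = 2 × SD² × (z₀.₉₅ + z₀.₉₀)² / (margin + 67)² = 2 × 138² × (1.645 + 1.282)² / 83.8² = 46.5, rounded up to 47. The noncentral t version gives 48. Both are within two of the stated 49, so the sample size matches an unadjusted comparison on the raw SD.

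At 49 per group:
- SE = 138 × √(2/49) = 27.88 s.
- Power = Φ(83.8/27.88 − 1.645) = Φ(1.361) = 0.913 (0.910 by noncentral t).

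At 55 per group power is 0.938.

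**Effect of adjusting for BMI**

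Let r be the within-arm correlation of BMI with performance time. **No value is given in the documents, so r is an assumption and is shown as a range.** The residual SD is 138 × √(1 − r²), the SE scales by the same factor, and the gain is equivalent to multiplying the sample by 1/(1 − r²).

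| Assumed r | SE, s | 95% CI half-width, s | CI narrower by | Power at 49 per group | n per group for 90% power |
|---|---|---|---|---|---|
| 0 | 27.9 | 54.6 | – | 0.913 | 47 |
| 0.1 | 27.7 | 54.4 | 0.5% | 0.916 | 46 |
| 0.2 | 27.3 | 53.5 | 2.0% | 0.923 | 45 |
| 0.3 | 26.6 | 52.1 | 4.6% | 0.934 | 43 |
| 0.5 | 24.1 | 47.3 | 13.4% | 0.966 | 35 |

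Power and n use the normal approximation. The noncentral t gives 0.93 at r = 0.3 and 0.96 at r = 0.5. In sample-size terms, r = 0.3 is worth 1/0.91 = 1.10 times the patients and r = 0.5 is worth 1/0.75 = 1.33 times.

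**If the true advantage were smaller than planned**

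With an assumed advantage of 40 s (not a figure from the plan), noncentral t power is 0.65 unadjusted, 0.68 at r = 0.3 and 0.76 at r = 0.5.

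**Chance imbalance in BMI**

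An imbalance of one standard error moves the unadjusted time difference by r × 27.88 s, which is 8.4 s at r = 0.3. This is not an extra error on top of the standard error, because 26.60² + 8.36² = 777 = 27.88². Adjustment removes this component; the unadjusted interval already allows for it.

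**Site**

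If the centres' mean times differ by D and one centre enrols a share p, site explains p(1 − p)D²/138² of the variance. With assumed p = 0.7, this is 1% for D = 30 s, 4% for D = 60 s and 9% for D = 90 s. The documents give neither D nor p.

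**The case against.** The strongest reply is that nothing here is wrong. The unadjusted test is valid, the sample size was computed for it, and it meets its power target at 49 per group. Chance BMI imbalance is already carried in its standard error and neither biases the estimate nor inflates the type I error. All of this stands.

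A reader might infer that the plan itself regards BMI as a likely influence on performance time and then ignores it, so that precision is certainly being thrown away. The text does not support that. It sets out to evaluate whether higher BMI has an influence, which is an open question, and no section states a BMI effect or estimates one. A reader might also conclude that adjustment would repair the mismatch between a 16.8 s margin and a 27.9 s standard error. It would not: at r = 0.3 the standard error is still 26.6 s.

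It can also be said that site has the better documentary claim to be in the model. That is correct, and a model with BMI alone would be an odd choice. One caution applies: a difference in familiarity between centres would act partly as an arm-by-site interaction, which a site main effect does not remove.

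Two points carry less weight. Covariates may be left to an analysis plan that is not shown, but the article does fix the primary method and does give BMI a role, so recommending a better use of it is not a complaint about missing detail. Changing a primary analysis with a quarter of the sample recruited and an unblinded statistician calls for care. No interim analysis is planned, however, so it can be done before outcomes by arm are examined.

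**Conclusion.** The point holds as a missed efficiency. The primary comparison is described without covariates, although BMI must be on file for every patient and site is the stratification factor. For assumed BMI-time correlations of 0.1 to 0.3 the confidence interval would narrow by about 0.5% to 5%, and power at 49 per group would rise from 0.91 to at most 0.93. Reaching 0.96 to 0.97 requires r = 0.5, for which the documents give no basis. If BMI is unrelated to performance time there is no gain, and almost no loss.

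These figures rest on the plan's SD, margin and expected means, and on a linear BMI effect of assumed size. Any gain from site comes on top and is equally undocumented. The validity of the planned test and the adequacy of the stated sample size for it are not in question.

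**What to change.** Before any results are examined, prespecify the primary analysis as a linear model of performance time on arm, site and continuous BMI. Judge non-inferiority on the adjusted RCB − ICB difference in means, with the margin and error rate unchanged, and report the unadjusted difference alongside as support. The same covariates may be added to the arm comparisons of needle visibility (through an ordinal model), needle passes and needle angle. The BMI subgroup analysis can remain as a separate question.

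The cost is two degrees of freedom (96 to 94 at 49 per group, which leaves the one-sided 5% t quantile at 1.661) and a short, dated amendment during recruitment stating that no outcome data by arm had been reviewed. No new patients are needed, and no new measurements, given that BMI is already required for the subgroup analysis.

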#### Interventions

Blocks will be performed by anaesthesiologists experienced in US-guided regional anaesthesia or by PGY-2 to PGY-5 residents under direct supervision by an experienced anaesthesiologist. Operators will have registered a minimum of 25 USG blocks before participating in the study.

Upon arrival in the induction room, standard ASA monitoring will be installed and an 18-gauge or 20-gauge intravenous catheter will be inserted in the contralateral arm. Premedication will be given based on patient preference and the anaesthesiologist’s judgment. Patients will be placed in the supine position with the torso elevated to about 30 degrees and the head facing the opposite side. After a prescan and US parameter optimization, the US probe will then be applied using a sterile technique. A high-frequency linear US probe (6–15 Hz Philips HD11XE Ultrasound; Philips Medical Systems, Bothell, WA, USA, 9–15 Hz Logiq P6; GE Healthcare, Mississauga, ON, Canada, or 15–6 MHz linear probe Sonosite Edge HFL50x; Sonosite Canada inc. Markham, Ontario, Canada) will be used and placed parasagittally just medial to the coracoid process and caudal to the clavicle. Short-axis visualization of the axillary vessels and of the cords will be obtained; the lung and second rib will be identified.

For the retroclavicular approach, the needle insertion point will then be found by palpating the supraclavicular fossa, just medial to the shoulder, at a point sufficiently posterior to the clavicle (generally 1–2 cm depending on morphology and the extent to which the supraclavicular fossa can be depressed) and medial to the trapezius muscle insertion point on the clavicle. This landmark is essential, as the needle will need to clear the clavicle and stay parallel to the US probe to avoid any posterior angling. From this finger position, probe rotation and alignment with the palpating finger will be perfectly achieved while keeping the axillary vessels in the short axis. Once probe rotation achieves finger-probe alignment, the needle will now aim more towards the anterior axillary line than with the coracoid ICB. For optimal imaging and technique the final probe position should rest in the delto-pectoral groove.

For coracoid ICB, the US probe will be applied in the infraclavicular fossa until good visualization of the axillary vessels is obtained and if possible, the brachial plexus cords, then the optimal approach angle and puncture point will be planned.

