### Auditing

No auditing is planned. If considered necessary by the research members, auditing on the quality of the data gathering might be conducted for the specific anaesthesiologist with whom atypical or incomplete data are obtained.

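### Performance time depends on who does the block, yet every named test leaves out operator and site; adding both is a cheap improvement, and whether the planned interval is too narrow depends on facts the protocol does not give

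*Protocol article*

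**What the plan says.** Statistical methods names the analyses. For the primary outcome, "performance time will be analyzed with a non-inferiority test of the averages". For continuous secondary outcomes it is the t test and, "if not, the Mann-Whitney test will be used". For ordinal outcomes, "for ordinal data the chi square test will be used if data are parametric, otherwise the Mann-Whitney test will be used". Chi-square or Fisher tests cover dichotomous outcomes. No operator or site term is named, and the Sample size section applies no design effect.

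On operators, the Interventions section says "Blocks will be performed by anaesthesiologists experienced in US-guided regional anaesthesia or by PGY-2 to PGY-5 residents under direct supervision", and "Operators will have registered a minimum of 25 USG blocks before participating in the study". That minimum counts ultrasound-guided blocks of any kind, not blocks by each approach.

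Under Allocation: sequence generation, patients are randomised individually "with a 1:1 allocation ratio" by a "computer-generated randomization schedule stratified by sites using permuted blocks of random sizes". The same section says that the two centres usually use opposite approaches. Risk of bias adds that more providers at the Sherbrooke centre are competent with the retroclavicular block (RCB), and that most patients will be enrolled there.

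Auditing foresees checks "for the specific anaesthesiologist with whom atypical or incomplete data are obtained", so data can apparently be traced to an individual. It does not show that operator is a coded variable.

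The protocol does not give the number of operators, blocks per operator, how an operator is assigned to a patient, or whether each operator does both approaches.

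**The concern.** Performance time is imaging time plus needling time, so it measures how fast the operator works. With a target of 55 per group, 110 blocks at two hospitals, some operators almost certainly contribute several; avoiding this would need about 110 different operators. Blocks by the same operator are likely to be correlated, while the named tests treat all patients as independent.

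The consequence depends on how operators relate to arms:

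- **Operators do both approaches, with the same approach effect for all.** Operator variance stays in the error term. The test keeps its level but may lose precision.
- **Operators lean to one approach after allocation.** The arms then partly compare different people, and the ordinary standard error is too small.
- **The approach effect differs by operator.** The standard error is again too small, even if everyone does both approaches. Uneven RCB competence makes this plausible.

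In the last two cases the risk is a false claim of non-inferiority against a margin of only 16.8 s.

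**Working it through.** **1. The plan's own figure.** Inputs from Sample size: infraclavicular (ICB) time 5 min 36 s = 336 s; RCB time 4 min 29 s = 269 s; difference −67 s; SD 2 min 18 s = 138 s; margin 5% × 336 = 16.8 s; one-sided 0.05; power 0.90.

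n = 2(1.645 + 1.282)² × 138² / (16.8 + 67)² = 46.4, so 47 per group (48 with the t distribution). The stated 49 is thus reproduced to within two patients, with patients taken as independent. At 49 per group, SE = 138 × √(2/49) = 27.9 s, 83.8/27.9 = 3.01, and power = Φ(3.01 − 1.645) = 0.91.

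**2. Assumed inputs (not in the protocol).** 8 to 22 operators; operator share of variance ρ of 5 to 30%; the routing of patients to operators; the spread of the approach effect between operators.

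**3. Both approaches as randomised, common effect.** With N = 98 patients and J operators, adjusting for operator changes the SE by about √(1 − ρ) / √((N − J)/(N − 1)). The second factor is the price of arms not being balanced within operator.

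- J = 12, ρ = 0.30: 27.9 × 0.837 / 0.942 = 24.8 s; power Φ(83.8/24.8 − 1.645) = 0.96.
- J = 12, ρ = 0.10: 28.1 s; power 0.91, no gain.
- J = 20, ρ = 0.20: 27.8 s; power 0.91, no gain.

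Simulated power agrees: 0.91 unadjusted and about 0.95 to 0.96 adjusted in the first case, 0.91 both ways in the other two.

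**4. One-sided error at the margin.** Simulation of 98 blocks, 4,000 runs per scenario, nominal 0.05. Adjusted means operator added as a main effect only.

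| Scenario | Operators | Unadjusted | Adjusted |
|---|---|---|---|
| Both approaches as randomised, ρ 0.30 | 8 / 12 / 20 | 0.052 / 0.048 / 0.051 | 0.052 / 0.049 / 0.049 |
| Routed 80:20 by approach, ρ 0.30 | 8 / 12 / 20 | 0.140 / 0.117 / 0.089 | 0.054 / 0.053 / 0.052 |
| Routed 80:20, ρ 0.10 | 8 / 12 / 20 | 0.088 / 0.082 / 0.066 | 0.044 / 0.051 / 0.046 |
| Routed 65:35, ρ 0.30 | 8 / 12 / 20 | 0.077 / 0.062 / 0.059 | 0.050 / 0.046 / 0.052 |
| Effect differs by operator, variance 10% of total, ρ 0.20 | 8 / 12 | 0.078 / 0.066 | 0.082 / 0.072 |
| Effect differs by operator, variance 20% of total, ρ 0.20 | 8 / 12 | 0.100 / 0.082 | 0.107 / 0.087 |

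The last two rows mean that the approach effect varies between operators with SD 138 × √0.1 = 44 s and 138 × √0.2 = 62 s. Adjusting for operator level alone does not help there.

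**5. Cross-check of the interaction by formula.** Take 11 operators with 10 blocks each, arms balanced within operator, ρ = 0.10, interaction variance 0.20, in units of total variance. True variance of the difference: 4(1 − 0.10 − 0.05)/110 + 0.20/11 = 0.0491. The ordinary test uses 4/110 = 0.0364. The SE ratio is √(0.0364/0.0491) = 0.86, so the error is 1 − Φ(1.645 × 0.86) = 0.078.

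**6. Extreme case: each operator does one approach only.** Design effect = 1 + (m − 1)ρ. With 110/11 = 10 blocks per operator and ρ = 0.10 it is 1.90. The error is 1 − Φ(1.645/√1.90) = 0.12, and power at 49 per group with a correct SE is Φ(3.01/√1.90 − 1.645) = 0.70. Over 8 to 22 operators and ρ of 0.05 to 0.20, the error is 0.07 to 0.19. This is a bound, not a forecast.

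**The case against.** The strongest objection is that centre habit does not create specialisation by arm. Allocation is 1:1 within each site, so each centre performs both approaches about equally whatever its custom. Operators become tied to arms only if someone chooses the operator after the envelope is opened, and nothing in the protocol says that happens. This stands: the routed rows are conditional. The other route to a small standard error, an approach effect that varies by operator, needs no routing and gains some support from the uneven RCB competence; its size is still assumed.

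A second objection is that lost precision is no defect, because the unadjusted test still has power 0.91 at the planned effect, above the 0.90 target. This also stands, so precision alone would not justify more than a suggestion.

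Third, operator adjustment may be set out in an analysis plan or full protocol not shown, and the data form may already carry an operator code. Either is possible. But the article does name its tests, and the point is about those tests.

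A reader might infer that the error bars are wrong whatever happens, and too wide whenever operators do both approaches. The documents do not support this. Randomisation is by patient and not balanced by operator, and the first row of the table shows an error of about 0.05 in that situation. A modestly wide interval (3 to 12% for ρ of 0.05 to 0.20) needs arms balanced within operator and no interaction.

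**Conclusion.** The point holds in conditional form, as a cheap improvement. Every named test omits operator, which plausibly drives the primary outcome, and site, on which randomisation is stratified.

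- With a common approach effect and operators doing both approaches as randomised, the planned interval is valid. Adjustment lifts power from 0.91 to about 0.95 with 12 operators and a 30% share, and does little or nothing at a 10% share or with 20 operators.
- With 80:20 routing, or an approach effect that differs by operator, the one-sided error is about 0.07 to 0.14 instead of 0.05. With 65:35 routing it is 0.06 to 0.08.

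All of these sizes rest on assumed operator numbers, variance shares and routing. That operators contribute several blocks each is an inference, though a safe one. No figure was computed for needle visibility or any other secondary outcome, so nothing is claimed about the size of an effect there.

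**What to change.** 1. Record a coded operator identifier and grade (resident or staff) on the data form, if not already there.
2. Analyse performance time with a linear mixed model: arm, site and operator grade as fixed effects, and operator as a random intercept. Judge non-inferiority on the adjusted difference against the same margin.
3. Add a sensitivity analysis with a random operator-by-approach term, or cluster-robust standard errors with a small-sample correction. The random intercept deals with routing but not with an approach effect that varies by operator.
4. Report the number of blocks per operator by arm, so that readers can see whether operators did both approaches.

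The cost is one coded field and some analysis wording; the sample size need not change for this. Trial status reports a quarter of the sample recruited, so operator may have to be filled in for those patients; the protocol keeps the hand-written forms. The statistician is not blinded, so the model should be fixed before any comparison by arm. The downside is a slightly more complex model, with some operators contributing few blocks and little gain if operators differ little.
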